### Data management

Data will be managed by the research team at the University of Sheffield following a DPIA with Sheffield Health Partnership University NHS Foundation Trust. Personal data will be stored separately from study data and will be used only to contact participants for the purposes of the research. All data will be anonymised before reporting and storing. After the study, all personal data will be deleted.

### Data analysis

Descriptive data for all demographic variables will be presented by trial arm to provide an overview of the cohort of participants recruited to the study, to evaluate the group allocation methods and to demonstrate the representativeness of the sample. Means and SD will be reported for the QoL and mental health measures. These will be compared with clinical cut-offs to indicate levels of well-being in the sample.

Eligibility rate, recruitment rate, completion rates and times for the strengths and needs assessment and the outcome measures will be reported descriptively. Sample medians will be used as an estimate of average completion times. CIs will indicate completion time variance.

Participants will be given 2 weeks to complete the strengths and needs assessment and the QoL/mental health measure questionnaire. After 1 week, they will be sent a reminder and offered support if they need it. After 2 weeks, they will be considered ‘lost to contact’ and will be sent a debrief form with links to support organisations. The number of participants ‘lost to contact’ or withdrawn will be recorded as part of the trial evaluation. If participants start but do not complete the strengths and needs assessment, we will record the time they spend on the assessment and the proportion completed. Any data previously given by participants who are ‘lost to contact’ or withdraw will still be analysed unless participants ask us to withdraw their data.

Preliminary effectiveness of the strengths and needs assessment will be assessed using mixed model analyses of covariance. These analyses will determine whether QoL (assessed using EQ-5D-5L and ReQoL-10) and mental health (assessed using PHQ-9 and GAD-7) changes between baseline and 3 months post-intervention are affected by allocation to the assessment/TAU group. The analyses will statistically control for demographic variables and clinical site. Effect size will be reported using partial eta-squared which will inform the sample size calculation for the definitive trial (RCT).

Qualitative data from the interviews and focus groups will be analysed using NVivo.^45^ Questions pertaining to acceptability and feasibility of the trial procedure will be analysed using thematic content analysis.^46^ Experience of post-diagnostic service provision more generally will be analysed using a reflexive thematic analysis approach.^47^

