The study will also evaluate the acceptability and feasibility of the trial design in preparation for a future definitive randomised control trial (RCT). The UK’s Medical Research Council’s framework for evaluating complex interventions^34^ highlights the importance of piloting prior to larger efficacy trials being carried out. This identifies potential problems which could lead to underpowering in larger trials and provides estimates for trial sample sizes. Acceptability will be evaluated in interviews with participants and focus groups with clinicians. The feasibility of the proposed recruitment, randomisation and data collection methods will be evaluated against a list of progression criteria before planning for a future trial.

Specifically, the research questions are

RQ1a: Are the proposed recruitment, randomisation and data collection methods acceptable and feasible for use within NHS adult autism diagnostic services?

RQ1b: Is the ICF CoreSets for Autism Strengths and Needs Assessment acceptable for use by autistic adults on receipt of an autism diagnosis?

RQ1c: What are the potential benefits or harms of completion of the ICF CoreSets for Autism Strengths and Needs Assessment?

The secondary aim is to gain a thorough understanding of the characteristics and mental health status of the populations receiving autism diagnoses in these clinical settings. We will use mental health and quality of life (QoL) outcome measures to answer the secondary research question:

RQ2: What are the demographics and current mental health status of adults being diagnosed in NHS services?

Mental health measures will also be used to monitor for adverse events arising from study participation. They will also provide preliminary data on whether the strengths and needs assessment improves well-being outcomes and how feasible it is to use these measures to measure efficacy in a larger trial.

The study will be reported according to Consolidated Standards of Reporting Trials guidelines for reporting randomised pilot and feasibility trials.^35^ If effective, the ICF CoreSets for Autism Strengths and Needs Assessment have the potential to be implemented in NHS diagnostic services as a standardised approach to providing post-diagnostic support for autistic adults.

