### Participants

The trial will recruit 72 autistic adults who have received a diagnosis of autism from one of the three participating clinical services (24 in each service). Participants will be adults (18+years) and will not have a diagnosis of a co-occurring learning disability. Clinicians will not invite individuals with a diagnosed intellectual disability to take part in the study. Participants will be recruited over a 6-month period from 1 April 2025 until 1 October 2025 or until the service target sample (24) has been recruited. The sample size is in line with guidance recommending a sample size of 70 for a two-arm randomised pilot study.^30^

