### Study procedures

Service users who receive a diagnosis of autism and meet the other eligibility criteria (18+ years old, no diagnosis of intellectual disability) will be given information about the study (written information leaflet, verbal information) by their diagnosing clinician which includes links to access further information about the study and contact details for the research team at the University of Sheffield. This will be given alongside other standard care information (eg, signposting to resources, information about their service’s post-diagnostic provision) at the appointment where they receive their diagnosis. The full information sheets for the study have been provided in standard and Easy Read/Plain English versions. Participants will have 4 weeks from the date of their diagnosis to decide whether they would like to participate in the study. They will be able to access a form to consent to participate and to provide their contact details via the links provided in the information leaflet.

Participants will be emailed a link to complete a short demographic questionnaire (age, gender, ethnicity, diagnosing service, date of diagnosis). Following this, they will be randomised into either the assessment group (n*=*36) or the treatment as usual group (n*=*36) by the research team at the University of Sheffield. This will be done using a minimisation approach which allows demographic factors to be balanced across groups in ongoing recruitment. This will be done using software developed by researchers at the University of York^36^ and will balance three factors (gender, age, ethnicity) with two levels for each factor (male/female, under/over 40, white/non-white) in each study arm. All participants will continue with the standard care offered by their clinical site during the study. This may include signposting to resources, follow-on appointments and psychoeducational input. It is not possible to blind participants to group allocation. However, clinicians will not be informed about individual participation or group allocation.

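### Planning the definitive trial on the pilot's partial eta-squared rests it on an unsigned, upward-biased and very imprecise effect estimate

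*Protocol article*

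**What the plan says.** The Data analysis section states: "Preliminary effectiveness of the strengths and needs assessment will be assessed using mixed model analyses of covariance". The outcomes are "QoL (assessed using EQ-5D-5L and ReQoL-10) and mental health (assessed using PHQ-9 and GAD-7) changes" from baseline to 3 months, and the article says the analyses will determine whether allocation affects them. On covariates: "The analyses will statistically control for demographic variables and clinical site". The effect size and its use follow: "Effect size will be reported using partial eta-squared which will inform the sample size calculation for the definitive trial (RCT".

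The Introduction gives the purpose of piloting: "This identifies potential problems which could lead to underpowering in larger trials and provides estimates for trial sample sizes".

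On size, the Participants section says "The trial will recruit 72 autistic adults", and Study procedures splits them equally, with "the treatment as usual group (n*=*36" as one arm. The basis is a rule of thumb: "The sample size is in line with guidance recommending a sample size of 70 for a two-arm randomised pilot study". The article gives no precision target for an effect, no minimally important difference, no confidence interval for the effect, and no choice among the four measures for sizing the later trial. Means and SDs are to be reported, but they are not linked to the sample size.

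**The concern.** The article states both the metric and its use, so this is not detail left to an analysis plan. Three properties make partial eta-squared a poor planning value here.

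- It cannot be negative, so it does not show the direction of a difference.
- Its expected value is above zero even when there is no effect, and above the true value when there is one.
- With 36 per arm or fewer its sampling error is large, and the required sample size varies with its inverse, which magnifies that error.

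It also depends on the covariates and the repeated-measures structure of the model, so it does not carry over cleanly to a trial analysed differently. Four measures will give four values, with no stated rule for choosing one.

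What is at stake is the size of the definitive trial. The article gives avoidance of underpowering as a reason to pilot, and this route could itself lead to an underpowered or needlessly large trial.

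**Working it through.** **The plan's own figure.** 3 services × 24 = 72 and 36 + 36 = 72, close to the guidance figure of 70. There is no power calculation to reproduce, and no size is stated for the definitive trial.

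**Inputs from the article.** 72 randomised 1:1; two-arm comparison; covariates age, gender, ethnicity and site; four outcomes.

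**Assumptions, because the article gives no values.** True d of 0.3 (also 0.5); 66 retained (33 per arm; 6/72 = 8% lost); two-sided 5% test; planned power 80% or 90%. Error df is N minus 7 (intercept, arm, age, gender, ethnicity, two site terms): 65 at N = 72 and 59 at N = 66.

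**Bias.** Partial eta-squared = F/(F + df). With no effect its mean is 1/(1 + df) = 1/66 = 0.015. For true d = 0.3 the true value is (d²/4)/(1 + d²/4) = 0.0225/1.0225 = 0.022. Simulation from the noncentral distribution gives a mean of about 0.04 (0.039 at N = 72, 0.040 at N = 66).

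**Precision.** The unadjusted 95% half-width on d is 1.96 × √(2/n): 0.46 at n = 36 and 0.48 at n = 33. If baseline adjustment used a T1–T2 correlation of 0.6 (assumed), multiplying by √(1 − 0.36) = 0.8 gives about 0.37 to 0.39 in raw-SD units.

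**Consequence if used as the planning value.** Each simulated partial eta-squared was converted to d = 2√(η²/(1 − η²)), then to n per arm = 2(1.96 + z)²/d², with z = 0.84 for 80% power or 1.28 for 90%. At d = 0.3 the correct size for 80% power is 2 × (2.80/0.3)² ≈ 174 per arm.

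| 66 retained, df 59 | True d = 0.3 | True d = 0.5 |
|---|---|---|
| Correct n per arm, 80% power | about 174 | about 63 |
| Planned n per arm, 10th to 90th percentile | 36 to about 3,300 | 20 to about 400 |
| Plans within a factor of two of the correct n | 33% | 49% |
| True power below 80%, planned at 80% | 54% | 55% |
| True power below 80%, planned at 90% | 46% | 43% |
| True power below 50%, planned at 80% | 34% | 25% |
| Estimated effect in the wrong direction | 11% | 2% |

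With all 72 retained, 34% of plans at d = 0.3 and 51% at d = 0.5 fall within a factor of two.

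**Comparison with using the pilot for the SD only.** If the target difference is set in advance, n varies with the square of the SD. With 64 df the 95% limits for the SD are 0.853 and 1.209 times the estimate, so n varies by factors of 0.727 to 1.462. For an illustrative target of 0.3 SD this is about 127 to 255 per arm around 174. That 95% range is far narrower than the 36 to 3,300 above, which covers only the middle 80% of plans.

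**The case against.** The strongest reply is that the article says the effect size will inform the calculation, not that it will be inserted unaltered. Other inputs are not excluded, and the later trial will have its own protocol and sample-size justification. This stands: the simulation shows what follows if the value is used as the planning value, not what the article commits the team to. But the article names no other effect input.

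Several stronger readings are tempting and should not be drawn.

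- **That an unsigned metric could lead to a large trial of something harmful.** The article also reports means and SDs, asks about benefits and harms, monitors the mental health measures for adverse events, and applies progression criteria before a future trial is planned. Partial eta-squared is not the gate.
- **That the route makes underpowering more likely than not.** This depends on the planned power: 54% at 80% but 46% at 90%, for d = 0.3. An unbiased but noisy estimate would also fall short about half the time when planning at 80%, so most of the problem is spread, and upward bias adds only a few points.
- **That the mean null value of 0.015 can be turned into a typical null sample size.** Sample size is strongly non-linear in partial eta-squared. The median plan under no effect is about 550 per arm at 80% power, and the spread is very wide.
- **That four tests imply a calculable false-positive rate.** The article states no significance threshold, and the four scales come from the same people and are related.

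On the claim to determine whether outcomes are affected, the surrounding text speaks of preliminary effectiveness and preliminary data, and the Discussion says a larger trial is needed. The verb is loose wording rather than a claim to a definitive answer.

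**Conclusion.** The concern holds as a weakness in a stated method: the article directs an unsigned, upward-biased and very imprecise statistic to the sizing of the definitive trial. If it served as the planning value at d = 0.3 with 66 retained, about two plans in three would miss the correct size by more than a factor of two, in either direction. At d = 0.5 about half would. The true effects, retention, error df, significance level and power are assumptions. The unadjusted interval of ±0.46 to ±0.48 would be narrower if baseline adjustment is strong.

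No number in the article is wrong. The pilot's size, conduct and primary outcomes (acceptability, usability and feasibility) are unaffected, and the consequence falls on a later trial. This is a should-fix point.

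**What to change.** Replace the sentence on partial eta-squared with the following.

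1. For each of the four measures, report the signed adjusted mean difference between arms with its 95% confidence interval, as an estimate and not as a test of effectiveness.
2. From the pilot, carry forward only the nuisance values for the definitive trial: the SD with its confidence limit, the T1–T2 correlation, and retention by arm. Planning on the upper one-sided 80% limit of the SD would mean multiplying the estimate by about √(64/54.3) = 1.085, which raises n by about 18% (1.085² = 1.18).
3. Set the target difference from a minimally important difference established outside the pilot, on one named primary outcome.
4. Say that the analyses will estimate the effect of allocation, in place of saying that they will determine whether there is one.

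The cost is a change to the analysis wording; no new data are needed. The downside is that the pilot no longer supplies an effect size for planning, so the team must justify a target difference from another source.

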Coreset development follows a rigorous protocol outlined by the WHO and aims to represent the perspectives of stakeholders.^25^ Following a process of consensus building with experts and autistic stakeholders, the CoreSets for autism and Attention Deficit Hyperactivity Disorder (ADHD) were published in 2019 and are available to guide clinical practice and research.^26^ In response to criticisms that there was a lack of guidance for professionals in how to apply the CoreSets^27^ and to move away from lists of codes, the ICF CoreSets platform was developed (icfcoresets.se). This is a user-friendly platform with a range of versions of the ICF CoreSet, for autism and ADHD (or combined), for different age ranges, and for self or proxy report. The CoreSet has reduced the number of functional codes from the full ICF framework to 110 (7% of all ICF codes).^28^ The most recent version of the online assessment has a total of 265 items derived from these ICF codes. In mitigation for the length of the assessment, the platform allows users to complete it in as many sittings as they wish, as responses are saved continually.

The online assessment has been evaluated for acceptability and feasibility of delivery in the UK and in Sweden and has been generally positively received by autistic people both for usability and for potential benefit. In the UK, it was piloted with groups of autistic adults for supported face-to-face completion (with a researcher, n=20) and for online self-completion (n=464). Acceptability and usability of the assessment were measured using the System Usability Scale (SUS)^29^ and the Theoretical Framework of Acceptability (TFA)^30^ and were found to be acceptable and usable for both supported and self-completion.^31^ The completion rate for autistic people was 91% and median completion time was 34 min, although times varied a great deal depending on the extent to which participants added additional text responses.

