### Primary outcome measures

The primary study outcomes are the acceptability and usability of the strengths and needs assessment, and the acceptability and feasibility of the trial procedures. Acceptability of the strengths and needs assessment will be measured using a single item from the TFA^30^: ‘How acceptable was the assessment to you?’. This is answered on a 5-point Likert scale from completely unacceptable to completely acceptable. The SUS^29^ will assess the usability of the assessment. This is a 10-item questionnaire answered on a 5-point Likert scale. Responses are summed and scaled to give an overall usability score which can be used to categorise interventions (eg, poor, ok, good, excellent). The SUS has demonstrated reliability and concurrent validity with measures of perceived and objective usability.^37^

Completion times for the strengths and needs assessment and outcome measures will be recorded and reported using sample medians. For those who drop out, time on task until drop-out will be recorded and reported.

The acceptability and feasibility of the trial procedures will be measured by collecting procedural data from the participating sites (eg, the number of participating clinicians, clinician time required to distribute participant invitations, service user eligibility rates). The study team at the University of Sheffield will collect data on recruitment rates and representativeness, adherence rates for the outcome measures and the attrition rate in each arm of the study. Participant interviews and clinician focus groups will also be used to evaluate the acceptability and feasibility of study procedures, barriers and facilitators to study participation, perceived value in the strengths and needs assessment, and any adverse events associated with the study.

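### The pilot's partial eta-squared is meant to inform the definitive trial's sample size, but it is unsigned, model-dependent and far too imprecise with at most 72 participants

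*Protocol article*

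**What the plan says.** The pilot is small. The Participants section sets the recruitment target: "The trial will recruit 72 autistic adults who have received a diagnosis of autism from one of the three participating clinical services (24 in each"; the figure 24 is per site. Study procedures splits the total equally: "assessment group (n*=*36) or the treatment as usual group (n*=*36"). The basis for that number is a rule of thumb: "The sample size is in line with guidance recommending a sample size of 70 for a two-arm randomised pilot study". No precision target for an effect estimate is given.

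Under Data analysis, mixed-model analyses of covariance will test whether allocation affects change from baseline (T1) to 3 months (T2) in "QoL (assessed using EQ-5D-5L and ReQoL-10) and mental health (assessed using PHQ-9 and GAD-7"), controlling for demographics and site. The section then fixes the effect measure and its use: "Effect size will be reported using partial eta-squared which will inform the sample size calculation for the definitive trial (RCT").

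The Introduction gives the reason for piloting: it finds problems that "could lead to underpowering in larger trials and provides estimates for trial sample sizes".

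The article names no minimum important difference, and it plans no signed difference with an interval. Means and SDs are to be reported, but the stated use is comparison with clinical cut-offs.

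**The concern.** Both the statistic and its use are written into the article, so this is not a detail left to an unseen analysis plan. Partial eta-squared suits that use badly for four reasons.

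- **It has no sign.** A benefit and a harm of equal size give the same value, although the article's own research questions ask about both.
- **It cannot be negative.** Its expected value is above zero when the true effect is zero.
- **It belongs to one model.** For an effect on change, it varies with the T1-T2 correlation and the covariates, so it does not carry over to a trial analysed in another way.
- **It is very imprecise at this sample size.** This is the main problem.

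At stake is the size of the next trial. The Introduction presents avoiding underpowering as a purpose of the pilot, and this use of the statistic can lead to just that, or to a trial far larger than needed.

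**Working it through.** **The plan's own figure.** 3 sites × 24 = 72 and 2 arms × 36 = 72, in line with the quoted 70. No alpha, power, SD or effect size is stated, so nothing further can be reproduced.

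**Inputs**
- Analysed n: 65, an assumption of about 10% loss (72 × 0.90 = 64.8). The article gives no T2 retention figure, because "the attrition rate in each arm of the study" is something the pilot will measure. The 91% in the Introduction is completion of the assessment in an earlier pilot, so it is not used. n = 58 and n = 72 (no loss) are also run.
- Error degrees of freedom: n − 7 (intercept, allocation, three demographic factors, two site contrasts), which is 58 at n = 65. This is an assumption about the model.
- Definitive trial: two-sided 5% and 90% power, assumed.
- True effect d: the allocation effect divided by the residual SD of the analysed contrast. No value is given; 0, 0.2, 0.3 and 0.5 are tried.
- The statistic is assumed to be converted directly into a sample size.

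**Formulas.** The 1-df F statistic is noncentral with λ = n·d²/4, and η² = F/(F + df). The implied effect satisfies d² = 4η²/(1 − η²), so the implied total is N = (1.960 + 1.282)² × (1 − η²)/η². The needed total is 4 × (1.960 + 1.282)²/d². For d = 0.3 this is 4 × 10.507/0.09 = 467. The ratio of implied to needed N does not depend on the power chosen.

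**No true effect, n = 65.** Mean η² = 1/(1 + 58) = 0.017, against a true value of 0.

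**True d = 0.3 (true η² = 0.0225/1.0225 = 0.022; 467 needed), by simulation**

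| Analysed n | Middle 80% of implied N | Under half of 467 | Over double 467 | Trial with under 80% power |
|---|---|---|---|---|
| 58 | about 90 to 9,200 | 36% | 32% | 47% |
| 65 | about 95 to 9,000 | 35% | 32% | 46% |
| 72 | about 100 to 8,700 | 34% | 32% | 46% |

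The last column is the share of pilots with implied N below 349, the number that gives 80% power at d = 0.3. At n = 65 the median implied N is about 400 and only 33% of pilots land within a factor of 2 of 467.

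**Other true effects, n = 65.** At d = 0.2, 43% of pilots imply under half the needed N and 30% over double. At d = 0.5 the shares are 26% and 25%.

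**Interval around one result.** An observed d of 0.3 at n = 65 gives η² of 0.025, with a 95% CI from 0 to 0.134. On the signed scale that is roughly −0.19 to 0.79.

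**Sign.** The chance that the pilot points the wrong way is Φ(−d√n/2). At d = 0.2 and n = 65 this is Φ(−0.806) = 21%. Each such pilot still gives a positive η².

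**Dependence on the correlation.** If change scores are analysed, a raw d of 0.3 becomes 0.3/√(2(1 − ρ)). At assumed ρ of 0.5, 0.7 and 0.8 that gives η² of 0.022, 0.036 and 0.053. The same difference in scale points therefore yields three different effect sizes.

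**What the pilot can estimate.** With 58 degrees of freedom the 95% CI for an SD is 0.85 to 1.22 times the estimate. For a fixed target difference, N scales with the square of the SD, so it is uncertain by about 0.72 to 1.49 times. Under η², the middle 80% alone spans about 0.2 (95/467) to 19 (9,000/467) times the needed N.

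**The case against.** The article says only that the statistic will inform the calculation. A reader might infer that the definitive trial will be sized from it alone and mechanically, but the text does not say so. The simulated sizes show what direct conversion would do. What stands is that no other source for the target effect is offered.

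Much of what a sound calculation needs is already planned: SDs for the measures and attrition by arm. The T1-T2 correlation could come from the same data. A wrong-direction result need not stay hidden from whoever plans the next trial, although η² itself does not show it. This makes the fix cheap, but it does not justify the stated use.

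Four stronger readings are not supported:

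- **Systematic inflation.** The upward bias is in the mean. At d = 0.3 the median implied N (about 400) is close to 467. With no true effect, putting the mean η² into the formula gives about 610 people, but the median null pilot implies about 1,300, so 610 is not typical.
- **Picking the largest of four outcomes.** Four effect sizes will exist and none is named for sizing, so selection is possible. Nothing says it will happen, and the choice of primary outcome ordinarily belongs to the next trial's protocol.
- **Correlation always makes the trial too small.** Against an unadjusted T2 comparison, the change-score conversion at ρ of 0.5, 0.7 and 0.8 gives 2(1 − ρ) = 100%, 60% and 40% of the needed N. Against a baseline-adjusted analysis it gives 2/(1 + ρ) = 133%, 118% and 111%. The direction depends on an analysis that the article does not specify.
- **The pilot itself is compromised.** Its primary outcomes are acceptability, usability and feasibility, and effectiveness is labelled preliminary.

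**Conclusion.** The concern holds as a planning flaw that should be fixed. It is not a fault that undermines the pilot. The article ties the definitive sample size to a statistic that a pilot of this size cannot estimate usefully. If it were converted directly at a true effect of 0.3, about two pilots in three (35% + 32% = 67%) would miss the needed number by more than a factor of 2, split almost evenly between too small and too large.

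The exact percentages rest on the assumed loss, model degrees of freedom and true effect. The conclusion does not: it is much the same from n = 58 to n = 72, and serious errors in both directions remain at true effects of 0.2 and 0.5. Imprecision is the main defect; lack of sign and dependence on the model add to it.

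**What to change.** Replace the partial eta-squared sentence in Data analysis with wording to this effect:

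1. For each of the four measures, the signed adjusted mean difference between arms is reported in scale points with a 95% CI.
2. The definitive trial's target difference is based on a minimum important difference for its intended primary outcome.
3. Only the SD (with its confidence limits), the T1-T2 correlation and retention by arm are carried forward from the pilot.
4. The pilot's interval is used only to check that the target difference is not ruled out.

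The cost is a change of wording. All the quantities come from data already being collected, and the change can still be made before analysis. The one real burden is that the target difference must be justified from outside the pilot.
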